**GENERAL INFORMATION**

This document describes the ‘Understanding changes in treatment-related regional bone turnover using 18F-fluoride-PET/CT (18F-PET/CT) in HIV-1-infected men: PETRAM study’, coordinated by the UCL Research Department of Infection and Population Health, and provides information about procedures for entering participants into it. Every care has been taken in drafting this protocol, but corrections or amendments may be necessary. Clinical problems relating to this study should be referred to the Chief Investigator.

**COMPLIANCE**

The study will be conducted in compliance with the approved protocol, the Declaration of Helsinki (fourth revision 1996) the principles of Good Clinical Practice (GCP), the UK Data Protection Act (DPA number Z5886415), the Commission Directive 2005/28/EC with the implementation in national legislation in the UK by Statutory Instrument 2004/1031 and subsequent amendments, and NHS research governance and other regulatory requirements, as appropriate in the participating centres.

**SPONSOR**

UCL is the Sponsor of this study. Queries relating to sponsorship of this study should be addressed via the study management team.

As a University organisation we use personally-identifiable information to conduct research to improve health, care and services. As a publicly-funded organisation, we have to ensure that it is in the public interest when we use personally-identifiable information from people who have agreed to take part in research. This means that when you agree to take part in a research study, we will use your data in the ways needed to conduct and analyse the research study. Your rights to access, change or move your information are limited, as we need to manage your information in specific ways in order for the research to be reliable and accurate. If you withdraw from the study, we will keep the information about you that we have already obtained. To safeguard your rights, we will use the minimum personally-identifiable information possible.

Health and care research should serve the public interest, which means that we have to demonstrate that our research serves the interests of society as a whole. We do this by following the UK Policy Framework for Health and Social Care Research.

If you wish to raise a complaint on how we have handled your personal data, you can contact our Data Protection Officer who will investigate the matter. If you are not satisfied with our response or believe we are processing your personal data in a way that is not lawful you can complain to the Information Commissioner’s Office (ICO).

Our Data Protection Officer is [name] and you can contact them at [contact].

**FUNDING**

An independent, academic grant in support of investigator initiated research from Gilead Sciences**.**

**STUDY REGISTRATION**

PETRAM study has been registered with EudraCT identified with the number 2017-000677-36.

SAE REPORTING

Following the standard PETRAM procedures.

Within 24 hours of becoming aware of an SAE, please email
the completed SAE form to the PI of the study  [[contact]](mailto:%[contact])

**study Administration**

Please direct all queries to the Chief Investigator.

**Summary of STUDY**

| **Summary Information Type** | **Summary Details** |
| --- | --- |
| **Short Title of Study** | PETRAM Study |
| **Version** | 4.0 |
| **Date** | 09 May 2021 |
| **EudraCT #** | 2017-000677-36 |
| **REC #** | 17/LO/2018 |
| **Clinical Trials.gov** | NCT03405012 |
| **Study Design** | This is a single centre, 48 week study to explore the pathogenesis of HIV treatment related bone disease by using a novel imaging technique, 18F-Fluoride Positron Emission Tomography/Computed Tomography (18F-PET/CT), which measures regional bone formation. The study will include other standard methods (serum bone markers and DXA) for comparison. Patients enrolled will have baseline, mid-study and end-of-study assessment, with baseline being the date of replacing tenofovir disoproxil fumarate (TDF) in their HIV treatment regimen with tenofavir alafenamide fumarate (TAF), compared to a control group continuing TDF. Allocation to change to TAF or continue TDF will be randomised to allow unbiased assessment of bone changes. |
| **Type of Participants to be Studied** | HIV-1-infected men aged 40-65 years of age, on an ART regimen containing rilpivirine (RPV)/TDF/ emtricitabine (FTC) for at least 6 months, with plasma HIV RNA (pVL) <50cp/mL and without any known history of osteoporosis. |
| **Setting** | Single clinical site: the Mortimer Market Centre, London, UK |
| **Groups to be Compared** | **Group 1 (TAF)**: Change ART to RPV/TAF/FTC (as the fixed dose combination; Odefsey® one tablet daily);  **Group 2 (TDF):** Continue current ART, RPV/TDF/FTC (as the fixed dose combination; Eviplera® one tablet daily). |
| **Study Hypothesis** | We hypothesise that there will be ongoing subclinical loss of bone at the hip and lumbar spine as measured by 18F-PET/CT in those remaining on TDF while in those changing to TAF there will be reversal of some of this subclinical loss on repeat imaging at the end of the study. This study is intended to determine if the improvement in bone mineral density is associated with an increase in bone formation (detected by a change in 18F-PET/CT measurement), or a reduction in bone loss (increase in bone mineral density but no change in 18F-PET/CT). |
| **Primary Outcome Measure(s)** | Change in regional bone formation at the hip and lumbar spine as measured by 18F-PET/CT between baseline and the last study scan. |
| **Secondary Outcome Measure(s)** | Change in regional bone formation at the hip and lumbar spine as measured by 18F-PET/CT at the mid-study scan. |
| **Exploratory Outome Measure(s)** | 1. To compare changes in volumetric bone formation measured by 18F-PET/CT between baseline, mid-point and last study scans. 2. To compare changes in bone mineral density at the hip as measured by DXA vs. 18F-PET/CT between baseline, mid-point, and last study scans. 3. To compare changes in bone mineral density at the lumbar spine as measured by DXA between baseline, mid-point, and last study scans. 4. To compare the changes in bone biomarkers with changes in 18F-PET/CT between baseline, mid-point, and last study scans. 5. To compare the changes in Trabecular Bone Score (TBS) and whole body (lean and fat mass measurements) from DXA between baseline, mid-point and last study scans. 6. To determine the changes in FRAX® score from baseline to the last DXA scan. |
| **Nos. of Participants** | 30 |
| **Duration** | 22-103 weeks (duration variable because of challenges presented by COVID-19 in 2020-2021) |
| **Sponsor** | UCL |
| **Countries of Recruitment** | UK |
| **Funder** | Gilead Sciences |
| **Chief Investigator** | [name] |

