# TDF is a prodrug of the nucleotide analogue tenofovir (TFV). Tenofovir alafenamide (TAF) is a phosphonoamidate prodrug of TFV, which undergoes conversion to TFV intracellularly, achieving higher active metabolite concentrations in peripheral blood mononuclear cells and lower plasma TFV exposures than TDF. TAF has demonstrated significantly less impact on renal and bone markers, compared to TDF [16-18]. Study GS-292-0109 showed that switching away from a TDF-containing regimen to a TAF-containing regimen resulted in significant improvements in spine and hip BMD as measured by DXA. In those switching to TAF vs. those remaining on TDF, BMD increased at both the spine (+1.79% vs. -0.28%; p<0.001), and the hip (+1.37% vs. -0.26%; p<0.001), respectively [19].

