# Our study is novel as we believe this is the first time that 18F-PET/CT will be used in HIV-infected patients. Importantly, this novel imaging technique has the capacity to provide important insights into the pathogenesis of HIV-treatment-related bone disease and longitudinal changes over time can be quantified. In HIV-infected individuals different types of bone disease may coexist and different aetiologies may be more readily differentiated than by conventional methods such as DXA. By using 18F-PET/CT it is hoped that it will be possible to determine if the improvement in bone density expected to be seen with changing patients to TAF, as compared to continuing with TDF, is associated with an increase in bone formation, detected by a change in 18F-PET/CT measurement, or a reduction in bone loss. In the latter case, there would be an increase in BMD but no change in 18F-PET/CT.

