**8.3. SAMPLE SIZE**

A total of 30 subjects (in order to have 30 evaluable subjects more than 30 may be randomised) will be randomised in a 1:1 ratio (15 subjects per group) into the two study groups. Assuming a mean increase from baseline of 25% in the plasma clearance of 18F-fluoride to bone tissue (Ki and SUV, primary outcome) in the TAF group and no change in the TDF group, and a standard deviation of 20% [17] then a total of 15 subjects in each group provide at least 90% power to detect a significance difference between groups with a Type-1 error of p=0.05. The actual power may be higher than this since the method of analysis (analysis of covariance, see below) is a more powerful technique than change from baseline.

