**8.4. ANALYSIS**

The primary analysis will compare the two groups as allocated (intention to treat, ITT). Analysis of covariance will be used to adjust for baseline value and the time interval between the baseline scan and the final scan. The need to include an interaction term between this time interval and treatment arm will be considered. Ki and SUV values may be transformed to conform with the assumptions in the statistical model (the transformation will be chosen before conducting any analyses stratified by randomised group). Point estimates will be accompanied by 95% confidence intervals. P values will not be adjusted for multiple comparisons [21].

Additional, exploratory analyses will compare the concordance between changes in bone loss as assessed by 18F-PET/CT, DXA, and biochemical markers. Although the different screens were planned to be conducted in the same week, this was also disrupted by the covid-19 epidemic. These analyses will therefore consider comparable screens in a window of ±12 weeks.

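### One of the two mechanisms is to be inferred from an unchanged PET result, but with 15 men per arm a null result cannot exclude a rise of about 15 points

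*Protocol*

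**What the plan says.** The Study Hypothesis entry in the protocol's summary states the purpose as a choice between two explanations for an improvement in BMD. The first is "an increase in bone formation (detected by a change in 18F-PET/CT measurement"). The second is "or a reduction in bone loss (increase in bone mineral density but no change in 18F-PET/CT"). Section 1.1 repeats the second pattern, framed as TAF compared with continuing TDF: "In the latter case, there would be an increase in BMD but no change in 18F-PET/CT". No third outcome, in which the mechanism stays undetermined, is named.

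Section 8.3 sizes the trial as follows: "Assuming a mean increase from baseline of 25% in the plasma clearance of 18F-fluoride to bone tissue" on TAF, no change on TDF, and an SD of 20%. It states that "a total of 15 subjects in each group provide at least 90% power", with the type I error set at 0.05. Section 8.4 plans an analysis of covariance comparing the arms, and adds: "Point estimates will be accompanied by 95% confidence intervals". The protocol contains no margin and no criterion for when PET counts as unchanged.

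**The concern.** A test for a difference can show that PET changed. Failing to show it does not establish that PET stayed the same. The reduced-bone-loss explanation rests on exactly that second kind of statement, and nothing in the protocol says what evidence would justify it. If the true rise in formation on TAF is moderate, well below the 25% used for planning, a null PET result is likely. Read with a BMD increase, it would then match the pattern that the protocol assigns to the other mechanism. At stake is the mechanistic conclusion that the summary and Section 1.1 give as the study's purpose. The primary between-arm comparison is not at stake.

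**Working it through.** **Inputs (Section 8.3).** Difference 25 points (25% on TAF, 0% on TDF), SD 20, n = 15 per arm, type I error 0.05. Sidedness is not stated; two-sided is assumed, in line with the planned 95% intervals.

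**The protocol's own figure.**
- SE of the difference = 20 × √(2/15) = 7.30 points.
- 25/7.30 = 3.42. Power is 91.1% by the two-sample t-test (noncentral t, 28 df) and 92.8% by the normal approximation.
- n per arm for 90% power = 2 × [20 × (1.960 + 1.282)/25]² = 13.5, so 14.

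The claim of at least 90% power with 15 per arm therefore reproduces.

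**Precision for one PET measure.** The 95% half-width is t(0.975, 28) × SE = 2.048 × 7.30 = 14.96 points. An observed difference of exactly zero would be compatible with a true rise of about 15 points, and 14.96/25 = 60% of the planning effect.

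**Chance of a non-significant result when there is a true rise (one measure, 15 per arm).**

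| True rise (points) | Power | Non-significant |
|---|---|---|
| 5 | 10% | 90% |
| 10 | 26% | 74% |
| 12.5 | 38% | 62% |
| 15 | 51% | 49% |
| 20 | 75% | 25% |
| 25 | 91% | 9% |

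**Chance of demonstrating no change when the true difference is zero.** The criterion is that the whole interval lies inside ± the margin (400,000 simulated trials, SD estimated from the data). The protocol gives no margin, so a range is shown.

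| Margin (points) | 95% interval | 90% interval |
|---|---|---|
| 10 | 0.03% | 0.6% |
| 12.5 | 1% | 8% |
| 15 | 9% | 29% |
| 20 | 51% | 70% |
| 25 | 82% | 91% |

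For an 80% chance with a margin of 15 points and a 90% interval, n per arm = 2 × [20 × (1.645 + 1.282)/15]² = 30.5, so 31. With the planned 95% interval it is 38.

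**Sensitivity.**
- If the covariates correlate 0.5 to 0.7 with the change (an assumption), the residual SD falls to 17.3 to 14.3 and the half-width to 13.0 to 10.7 points.
- If only 13 per arm are evaluable (an assumption; Section 8.2.1 mentions withdrawals but gives no number), the half-width widens to 16.2 points and power for 25 points falls to 86%.

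**The case against.** Several points on the other side have force.

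- **The rule is not stated as a p-value rule.** A reader might infer that the protocol treats a non-significant difference as no change. It nowhere says so. Section 1.1 reasons from mechanism to expected pattern and speaks of what is hoped, and Section 8.4 commits to confidence intervals that would show the ±15 points. This stands. The point is that a conclusion is tied to an unchanged PET result, while the only planned comparison cannot establish one for moderate effects.
- **A moderate rise would not usually be reported as the opposite mechanism.** A reader might infer that it would. The second pattern also requires a BMD increase. For illustration only, the cited switch trial reports that "BMD increased at both the spine (+1.79% vs. -0.28%; p<0.001), and the hip (+1.37% vs. -0.26%; p<0.001), respectively", which gives differences of 1.79 + 0.28 = 2.07 and 1.37 + 0.26 = 1.63 points. With an assumed BMD SD of 3%, which the protocol does not give, power is 45% and 30%. At a true 10-point PET rise, and assuming independence, both conditions are met in 0.74 × 0.45 = 33% (spine) or 0.74 × 0.30 = 22% (hip) of trials. SUV and Ki at two sites are all primary, so the chance that every one is non-significant is at most the single-measure figure.
- **Direction.** The word change might be taken to count a fall in Ki as increased formation. It sits inside a phrase about an increase in formation, so the text does not support that reading.
- **TDF arm.** The hypothesis expects continuing loss on TDF, while Section 8.3 assumes no change. That is a conservative planning assumption, since a fall on TDF would widen the difference. It is not a contradiction.
- **Other evidence.** Bone markers (Section 6.5) and concordance analyses (Section 8.4) also bear on mechanism. This helps, but the summary and Section 1.1 define the two mechanisms by PET and BMD alone.
- **The SAP may set a criterion.** It may, and the absence of a margin is not itself the complaint. A margin in the SAP would not narrow the interval, and recruitment is complete (Section 6.2). The hypothesis would still offer only two outcomes.

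**Conclusion.** The point holds in limited form. As worded, the hypothesis lets reduced bone loss be concluded from a null PET result that this design can support only for large effects. On the planning figures, with a two-sided test, one PET measure and no covariate gain, the trial can exclude a difference of about 25 points if the true difference is zero (82% of the time with the planned 95% interval, 91% with a 90% interval). It cannot reliably exclude 15 points or less (9% and 29% at ±15). It would therefore be too strong to say that 15 per arm can never support a finding of no change. Plausible covariate gains narrow the interval but leave it above 10 points. The sample-size arithmetic is sound. This is a cheap and worthwhile correction to how the result may be interpreted, not a flaw that invalidates the trial.

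**What to change.** In the Study Hypothesis entry, in Section 1.1 and in Section 8.4:

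- State that a non-significant PET difference is inconclusive on mechanism.
- Allow no change, and hence reduced bone loss, to be concluded only if the planned confidence interval for the between-arm Ki/SUV difference lies wholly within a justified margin. Fix the margin before arm-level data are seen. Section 8.4 already sets a similar point in time for choosing the transformation.
- Give the margin on the scale of the analysis, and say which of the primary PET measures must meet it.
- In all other cases without a demonstrated PET increase, report the mechanism as not determined.
- Note that, on the planning figures, only differences near 25% can be reliably excluded.

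The cost is wording only: the intervals are already planned, and no further participants, scans or tests are needed. The drawback is that a null PET result becomes inconclusive instead of a positive mechanistic claim.

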**Abbreviations**

18F-PET/CT 18F-fluoride Positron Emission Tomography

AE Adverse Event

AR Adverse Reaction

AIDS Acquired Immunodeficiency Syndrome

ART Antiretroviral therapy

BMI Body Mass Index

BMD Bone mineral density

cART Combination Antiretroviral Therapy

CI Chief Investigator

COVID-19 Coronavirus Disease 2019

CRF Case Report Form

CT Computed Tomography

CTA Clinical Trial Authorisation

DSUR Development Safety Update Report

DXA Dual-energy X-ray absorptiometry

eGFR Estimated glomerular filtration rate

FBC Full blood count

FRAX Fracture Risk Assessment Tool

FTC Emtricitabine

GCP Good Clinical Practice

HBV Hepatitis B Virus

HCV Hepatitis C Virus

HIV-1 Human Immunodeficiency Virus Type 1

KCL King’s College London

Ki plasma clearance of 18F-fluoride to bone tissue

mSv millisieverts

PI Principal Investigator

PIS Participant Information Sheet

PET Positron Emission Tomography

rpm Revolutions per minute

QA Quality Assurance

QC Quality Control

R&D Research and Development

REC Research Ethics Committee

RPV Rilpivirine

SAE Serious Adverse Event

SAP Statistical Analysis Plan

SARS-CoV-2 Severe Acute Respiratory Syndrome Coronavirus -2

SoC Standard of Care

SPC Summary of Product Characteristics

SUV Standardised Uptake Value

TAF Tenofovir alafenamide fumarate

TBS Trabecular bone score

TDF Tenofovir disoproxil fumarate

TMF Trial Master File

TMG Trial Management Group

TMT Trial Management Team

vBMD Volumetric BMD

VL HIV Viral Load

UCL University College London

UPCR Urine Protein: Creatinine Ratio

**1.** **BACKGROUND**

# The life expectancy of HIV-infected patients continues to improve due to antiretroviral therapy (ART). However, one of the side-effects of ART, particularly regimens containing the drug tenofovir disoproxil fumarate (TDF), is bone loss [1]. This bone loss is of concern because patients are starting treatment earlier, the HIV-positive cohort is ageing, and patients will be exposed to ART over very long periods.

# Our understanding of the pathogenesis of bone loss in HIV-infected patients on ART is incomplete. Moreover, there are likely to be several contributing factors including age-related bone loss, vitamin D deficiency, corticosteroid-induced loss, nutritional deficiency, as well as specific ART effects. Teasing out these different and/or multiple pathways leading to bone loss is critically important, as it will allow us to refine the diagnosis of the type of bone disease in a patient, ensuring that the correct treatment is given, and in some cases avoiding unnecessary changes in ART. Currently available methods to assess bone disease are limited to serum bone markers which provide a global assessment of bone turnover, bone biopsies which are limited to a single biopsy site and too invasive for widespread or repeated assessments, and changes in bone mineral density (BMD) measured using dual-energy X-ray absorptiometry (DXA). DXA gives 2-dimensional information, which correlates with fracture risk at the hip and spine, but it cannot elucidate the exact mechanism of the bone loss at those sites. In particular, it is unable to measure bone turnover at trabecular and cortical rich sites.

# 18F-fluoride positron emission tomography/computed tomography (18F-PET/CT), a novel functional imaging technique, allows the non-invasive quantitative assessment of bone mineralisation at specific clinically-important fracture sites [2]. It provides much more information than simple measures of bone mineral density, such as DXA, and offers several advantages over bone biopsy, and bone turnover markers, because it allows a direct measurement of bone formation at sites such as the spine and hip [3]. This allows an insight into the changes in bone turnover which may lead to an increased risk of fracture at these sites.

#

# **1.1. 18F-FLUORIDE PET/CT SCANNING PLATFORM**

#

# 18F-PET/CT imaging allows the quantitative assessment of regional bone formation – SUV and Ki. SUV is a measure of bone metabolic activity that assumes uniform distribution of the scan tracer whilst ki is a measure of bone metabolic activity and mineralisation that incorporates the blood concentration of the trace. Ki is measured in units of mL.min-1.mL-1 [4, 5]. The technique has been validated in the non-HIV setting by comparison with bone histomorphometric indices with significant correlations observed between regional skeletal kinetic parameters using 18F-PET/CT and the bone formation and mineral apposition rate [6, 7]. Furthermore, 18F- PET/CT has been developed and validated by [name] group at KCL as a tool to investigate regional bone metabolism in subjects with metabolic bone disease [8-10] and evaluate the response to current and novel therapies [11-13]. The method has shown important differences in remodelling activity between cortical and trabecular rich sites [14]. The technique is highly acceptable to patients, with short scan times and radiation exposure well within acceptable limits as set by the UK guidelines from the Administration of Radioactive Substances Advisory Committee (ARSAC) [15].

# TDF is a prodrug of the nucleotide analogue tenofovir (TFV). Tenofovir alafenamide (TAF) is a phosphonoamidate prodrug of TFV, which undergoes conversion to TFV intracellularly, achieving higher active metabolite concentrations in peripheral blood mononuclear cells and lower plasma TFV exposures than TDF. TAF has demonstrated significantly less impact on renal and bone markers, compared to TDF [16-18]. Study GS-292-0109 showed that switching away from a TDF-containing regimen to a TAF-containing regimen resulted in significant improvements in spine and hip BMD as measured by DXA. In those switching to TAF vs. those remaining on TDF, BMD increased at both the spine (+1.79% vs. -0.28%; p<0.001), and the hip (+1.37% vs. -0.26%; p<0.001), respectively [19].

